#### Part II: delivery of the vestibular rehabilitation programme

Those patients who require vestibular physiotherapy will enter the second part of the study. Alternatively, for patients not eligible for vestibular physiotherapy, the DSS will propose an alternative management plan, such as pharmacological treatment or a dietary intervention. Independently of the management plan applied, all patients will be reviewed after 3-month follow-up by the overseeing expert.

Once the diagnosis and treatment plan are agreed, patients requiring the vestibular rehabilitation programme will receive a 3-month treatment as explained below:*+ DSS group*: Patients will be seen by a non-specialist physiotherapist on a monthly basis over a 3-month period. This treatment will consist of customised vestibular exercises. Such exercises are based on the eye, head and postural exercises that provoke a patient’s symptoms. Exercises incorporating gaze fixation, head movements and postural exercises are prescribed to promote adaptation of vestibulo-ocular reflex and vestibulospinal reflex function. The patient will practice up to five exercises at home for approximately 1–2 minutes each, twice daily, initially at a slow speed and gradually increasing as symptoms improve. Patients presenting with vestibular migraine will perform a maximum of three exercises. These exercises will be chosen by the DSS from among a range of established exercises.*− DSS group*: Participants will receive routine vestibular physiotherapy as per standard current practice. The standard rehabilitation programme might include lifestyle advice and education, sometimes accompanied by a leaflet.

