#### Part I: diagnosis and management plan assessment

On the day of recruitment, patients will initially be examined by the non-specialist doctor, either with or without the DSS, according to randomisation result. In both the + DSS and − DSS groups, each patient will undergo the investigations required, following which the non-specialist doctor will formulate an initial diagnosis and management plan. The patient will then be invited to attend a specialist neuro-otology clinic, where they will be seen by an overseeing expert to undergo a gold standard diagnostic process and to determine the management plan appropriate to the diagnosis, which will be compared with the management plan previously advised by the non-specialist doctor. The overseeing expert will review investigations carried out and results assessed by the non-specialist doctor. In the event that the doctor’s assessment differs from the conclusion of the expert, the latter will decide on the final diagnosis and management plan of the patient according to current evidence-based guidelines.

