### Statistical analysis

Data analysis will be performed using SPSS version 16.0 software (SPSS, Chicago, IL, USA) and the StatXact statistical software package (Cytel, Cambridge, MA, USA). Statistical significance will be set to 0.05. Descriptive statistics will be calculated and presented. Comparisons which will be made include the following:Proportion of correct diagnosis by specialists to non-specialists and treatments with and without DSS use according to the overseeing expert’s diagnosis and treatmentComparison of the number of laboratory investigations prescribed with and without DSS useComparison of the number of investigation referrals with and without DSS useComparisons of improvement according to the patient at baseline and after 3 months of follow-up, based on the following tool scores: Dizziness Handicap Inventory, EQ-5D-3 L Questionnaire, visual analogue scale scores before and after treatment in the DSS vs. non-DSS user groups

For categorical values (e.g., referral rate), the chi-square test will be used for comparisons between groups. The Bonferroni correction will be used in cases of multiple comparisons. Normality will be tested with the Kolmogorov-Smirnov test. If normality is met, Student’s *t* test will be used. If not, a non-parametric Mann-Whitney *U* test will be used instead. For comparisons before and after treatment, a paired *t* test will be used regarding numeric data (e.g., questionnaire scores) after normality testing.

Because of the close monitoring of all study participants, the proportion of missing data is not expected to be substantial. In the unlikely event that more than 10 % of values corresponding to primary outcome measures are missing, recruitment will be extended to collect additional data.

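### Part II compares DSS-supported management, with its protocol-specified rehabilitation delivery, against routine management; it does not isolate the treatment the DSS proposed, as the secondary objective claims

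*Protocol article*

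**What the plan says.** All places are in the Protocol article.

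- **Secondary objectives.** One of the five is the effectiveness of the treatment the DSS proposes against that proposed by the non-specialist doctor working without it.
- **Part I.** Where the non-specialist's assessment and the expert's differ, "the latter will decide on the final diagnosis and management plan of the patient according to current evidence-based guidelines". Under Part II, rehabilitation begins once diagnosis and plan are agreed.
- **Part II, both arms.** "patients requiring the vestibular rehabilitation programme will receive a 3-month treatment as explained below". Patients not suited to vestibular physiotherapy follow another plan, and everyone is reviewed at 3 months.
- **Part II, +DSS arm.** Provider and schedule are fixed: "Patients will be seen by a non-specialist physiotherapist on a monthly basis over a 3-month period". So is the content: "This treatment will consist of customised vestibular exercises". Patients practise at home twice daily. On the role of the DSS: "These exercises will be chosen by the DSS from among a range of established exercises".
- **Part II, −DSS arm.** Delivery is left to usual care: "Participants will receive routine vestibular physiotherapy as per standard current practice". The content is left open as well: "The standard rehabilitation programme might include lifestyle advice and education, sometimes accompanied by a leaflet".
- **Statistical analysis, fourth comparison.** Patient-reported improvement from baseline to 3 months on the Dizziness Handicap Inventory, the EQ-5D-3L and "visual analogue scale scores before and after treatment in the DSS vs. non-DSS user groups".

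**The concern.** The objective names a narrow contrast: one source of treatment proposals against another. The Part II arms set up a wider one. The +DSS arm carries a stated provider, a stated contact schedule and a guaranteed structured programme. The −DSS arm carries whatever routine practice supplies. If routine delivery departs from the +DSS specification, that departure travels with the allocation and cannot be separated from the DSS.

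The outcomes are reported by patients, and the Blinding section lists only the recruiting research nurse and the overseeing experts as blinded. Regular scheduled contact could raise self-reported scores, and a less specialised provider could lower them. A positive result could therefore be credited wrongly to the DSS's proposals, and a null result wrongly held against them. The Discussion already counts better quality of life among the platform's advantages for patients, so the 3-month scores are likely to be read this way.

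**Working it through.** **Step 1. Set the arms side by side (Part II section).**

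| Element | +DSS | −DSS | Reading |
|---|---|---|---|
| Duration | 3 months | 3 months | Common to both |
| Physiotherapist | Non-specialist | Not stated | Specified in one arm only |
| Contacts | Monthly | Not stated | Specified in one arm only |
| Home programme | Customised, twice daily | Not guaranteed; advice, education and a leaflet are possibilities | Guaranteed in one arm only |
| Choice of exercises | Made by the DSS | Routine practice | The DSS output under test, so not a separate confounder |

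Within rehabilitation, the choice of exercises is the only element the section attributes to the DSS. Provider, contacts and the guarantee of a programme are set by the protocol.

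**Step 2. Follow the plan from proposal to delivery.** The objective refers to proposed treatment. Under Part I the expert has the last word in either arm, and Part II starts from the agreed plan. Where expert and non-specialist disagree, the treatment delivered is not the one the non-specialist proposed, with or without the DSS. This separates the 3-month scores from the proposals by a second route, independent of delivery.

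**Step 3. State what is estimated.** Randomisation protects the contrast between arms as managed: DSS-supported management, including its specified rehabilitation delivery, against routine management, under an expert-settled plan in both. It does not identify the effect of the DSS's proposals alone.

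**Step 4. Illustrate the consequence.** The plan has no figure to reproduce: the Sample size section says no formal calculation was made, for want of a standard deviation.

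Inputs:
- Part II runs in the UK and Greece only (Schedule of intervention), with 50 patients per country (Sample size) and 1:1 allocation (Sequence generation). The ceiling is 2 × 50 / 2 = 50 per arm.
- 25 per arm is an assumption, for the case where half of that number contribute.
- The significance level is 0.05 (Statistical analysis). Two-sided testing is assumed.
- The shift d due to delivery alone, with no DSS effect, is assumed to be 0.1 to 0.4 SD. Nothing in the document anchors it.

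Formula (normal approximation): SE = √(2/n) in SD units; rejection probability = Φ(d/SE − 1.96) + Φ(−d/SE − 1.96).

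SE = √(2/50) = 0.200 at 50 per arm, and √(2/25) = 0.283 at 25 per arm.

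| d (SD) | 50 per arm | 25 per arm |
|---|---|---|
| 0.1 | 7.9 % | 6.4 % |
| 0.2 | 17.0 % | 10.9 % |
| 0.3 | 32.3 % | 18.6 % |
| 0.4 | 51.6 % | 29.3 % |

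The Statistical analysis section applies Bonferroni to multiple comparisons without defining the family. If the family is the three instruments, the level is 0.05/3 = 0.0167 and the critical value 2.394. The ranges become 3 % to 35 % at 50 per arm and 2 % to 16 % at 25. If provider and contact effects cancel, d is near 0 and rejection stays near the nominal level.

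**The case against.** The strongest case on the other side has five parts.

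1. *The arms are not shown to differ in delivery.* A reader might infer that control patients see a different type of physiotherapist or attend on a different schedule. The article does not say so. It is silent on both for the −DSS arm, and routine care might also be monthly and given by non-specialists. A condensed article may leave such detail to the full protocol. This stands, and it is why the point is put as elements neither specified nor held equal. It does not restore the objective's wording, because nothing in the text equalises delivery.
2. *Programme content is the intervention.* This stands for the choice of exercises. It does not cover the guarantee of a structured, regularly reviewed programme.
3. *A pragmatic comparison with routine care is legitimate.* Agreed, and randomisation keeps it valid. The wording of the fourth comparison in the Statistical analysis section is itself neutral. Only the attribution in the Secondary objectives is at fault.
4. *The rejection rates say little about this trial.* They are generic values for assumed shifts at an uncorrected level. This stands; they are illustrations, and the conclusion does not depend on them.
5. *Little is at stake.* This is one secondary objective in a feasibility study. That limits the weight of the point but does not remove it.

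**Conclusion.** The point holds in a limited form. As written, the 3-month comparison estimates the effect of a package against routine management, under a plan the expert has settled in both arms. It does not isolate the treatment proposed by the DSS.

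Two stronger readings are not supported. The document does not establish that provider and schedule actually differ between arms, and the comparison is not invalid: it answers a broader question than the one the objective names.

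The point is minor to moderate. It touches one secondary objective, in two countries, with at most 50 patients per arm. The primary agreement outcome is unaffected, since it compares the non-specialist's initial diagnosis and plan with the expert's. The 8 % to 52 % range at 50 per arm (6 % to 29 % at 25) rests entirely on the assumed shift and on an uncorrected two-sided 5 % test. The direction of any delivery effect is unknown.

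**What to change.** 1. In Secondary objectives, reword the effectiveness item along these lines: *DSS-supported management and rehabilitation package versus routine management (UK and Greece)*. Interpret the fourth comparison under Statistical analysis in the same terms.
2. Keep patients on non-rehabilitation plans in that comparison. Part II follows them too, and a wording confined to rehabilitation would drop them.
3. State that no effect will be attributed to the DSS's treatment or exercise proposals alone.
4. If the CRF (not shown) does not already capture it, record in both arms the number of physiotherapy contacts, the provider type and whether a home programme was given. Report these by arm beside the 3-month scores.

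No change to either arm's care is proposed. The cost is a narrower secondary claim, some rewording and at most one short CRF item. The record of rehabilitation received would also help in planning the large-scale trial that this study is meant to inform.

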#### Follow-up

All participants will be reviewed after 3 months from their inclusion in the trial for a follow-up appointment with the specialist doctor.

### Criteria for discontinuation and end-of-study definition

Participants can withdraw from the trial at any time or if, in the opinion of the investigator or clinical team, it is medically necessary to do so. Reasons for withdrawal will be documented; participants who withdraw will be returned to routine care, and no further data will be collected. In the case of adverse events, these will be recorded in the medical records, and an adverse event form will be completed and emailed to the sponsor within the next 5 working days. When the last enrolled participant has completed the follow-up, the research ethics committee (REC) will be notified of the trial completion. The final study report will be completed within 12 months after trial completion.

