### Trial objectives

#### Primary objectives

The primary objectives of this study are (1) to determine whether the EMBalance DSS is an accurate supportive tool for the diagnosis and management plan of dizziness and/or balance disorders when used by non-specialist doctors and (2) to establish the feasibility of testing the DSS in a large-scale RCT. These objectives will be measured as follows:Percentage of agreement between the diagnosis and management plan established by the non-specialist doctors (using the DSS and not using the DSS) and the gold standard as determined by an overseeing expert and according to current evidence-based guidelines for the diagnosis and/or management of these disorders

The primary outcome assessment criteria are shown in Table 3.

**Table 3 Tab3:** Primary outcome assessment criteria

Diagnosis (Dx)				
Single		Concurrent		
If doctorDx = expert Dx	100 %	If doctorDx_1_ + Dx_2_ = expertDx_1_ + Dx_2_		100 %
If doctorDx ≠ expert Dx	0 %	If doctorDx_1_ + Dx_2_ ≠ expertDx_1_ + Dx_2_		0 %
		If doctorDx_1_ = expertDx_1_ and doctorDx_2_ NA/≠ expertDx_2_		50 %
Management (Mng)				
Single		Multiple		
If doctorMng = expertMng	100 %	Maximum number of correct Mng plans = 2	If doctorMng_1,2_ = expertMng_1, 2_	100 %
If doctorMng ≠ expertMng	0 %		If doctorMng_1,2_ ≠ expertMng_1,2_	0 %
			If doctorMng_1_ = expertMng_1_ and doctorMng_2_ NA/≠ expertMng_2_	50 %
		Maximum number of correct Mng plans = 3	If doctorMng_1,2,3_ = expertMng_1,2,3_	100 %
			If doctorMng_1,2,3_ NA/≠ expertMng_1,2,3_	0 %
			If doctorMng_1_ = expertMng_1_ and doctorMng_2,3_ NA/≠ expertMng_2,3_	33.3 %
			If doctorMng_1,2_ = expertMng_1,2_ and doctorMng_3_ NA/≠ expertMng_3_	66.6 %
		Maximum number of correct Mng plans = 4	If doctorMng_1,2,3,4_ = expertMng_1,2,3,4_	100 %
			If doctorMng_1,2,3,4_ ≠ expertMng_1,2,3,4_	0 %
			If doctorMng_1_ = expertMng_1_ and doctorMng_2,3,4_ NA/≠ expertMng_2,3,4_	25 %
			If doctorMng_1,2_ = expertMng_1,2_ and doctorMng_3,4_ NA/≠ expertMng_3,4_	50 %
			If doctorMng_1,2,3_ = expertMng_1,2,3_ and doctorMng_4_ NA/≠ expertMng_4_	75 %
Diagnosis		100 % = correct		
		50 % = half correct		
		0 % = incorrect		
Management		100 % = fully correct		
		>50 % = majority correct		
		50 % = half correct		
		<50 % = partially correct		
		0 % = incorrect		

These criteria determine the level of agreement between the non-specialist doctor and the overseeing expert

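### The withdrawal rule ends all data collection even for patients withdrawn on medical grounds, which can leave avoidable gaps, mainly in the 3-month outcomes

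*Protocol article*

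**What the plan says.** The section on criteria for discontinuation gives two routes out of the trial, the patient's own decision and a clinical one: "Participants can withdraw from the trial at any time or if, in the opinion of the investigator or clinical team, it is medically necessary". It keeps one item about the departure, "Reasons for withdrawal will be documented", and then sets a single consequence for both routes: "participants who withdraw will be returned to routine care, and no further data will be collected".

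Other sections promise complete assessment. The text under Overseeing experts says that every patient's case is reviewed by an expert. Part II says: "Independently of the management plan applied, all patients will be reviewed after 3-month follow-up by the overseeing expert". The Follow-up section says: "All participants will be reviewed after 3 months from their inclusion in the trial for a follow-up appointment with the specialist doctor". None of these makes an exception for withdrawn patients.

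The primary measure is "Percentage of agreement between the diagnosis and management plan established by the non-specialist doctors" and the expert's gold standard. The 3-month measures, listed under Statistical analysis, are the Dizziness Handicap Inventory, the EQ-5D-3L and visual analogue scales. That section expects few missing data. If more than 10 % of primary outcome values are missing, its response is that "recruitment will be extended to collect additional data".

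**The concern.** Ending data collection is right when a patient withdraws consent to it. It is not a necessary consequence when the investigator or clinical team takes the patient out because "in the opinion of the investigator or clinical team, it is medically necessary to do so". That patient may be willing to complete a questionnaire or attend the expert clinic, yet the rule forbids collecting the result. The trial imposes this loss on itself, and no later analysis plan can recover data that were never collected.

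Medical withdrawal plausibly goes with worse symptoms or a case that proved serious, so the missing values may be informative. They may also differ by arm. In Part II the two groups receive different rehabilitation. Only the recruiting nurse and the overseeing experts are blinded, while the non-specialist doctor receives the allocation envelope, so some of those who can prompt a withdrawal may know the arm. At stake is the between-arm comparison of improvement at 3 months and, to a smaller extent, the agreement outcome. Because the trial is meant to establish whether a large randomised trial is feasible, the rule could also be carried forward into that trial.

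**Working it through.** **1. Who the rule covers.** The sentence on withdrawal names both routes, and the next sentence applies to participants who withdraw, without distinction. Stopping study procedures is nowhere separated from withdrawing consent to data collection.

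**2. What is lost, by time of withdrawal.** Part I has the non-specialist examine the patient on the day of recruitment and form a diagnosis and plan. The expert assessment follows at a separate clinic. Part II treatment starts only once diagnosis and plan are agreed. The rule bars further data and does not delete data already held. Hence:

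| Withdrawal occurs | Primary agreement outcome | 3-month questionnaires |
|---|---|---|
| Before the expert visit | lost | lost |
| After the expert visit, before 3 months | kept | lost |

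The 3-month outcomes are exposed throughout, the primary outcome only in the first interval.

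**3. What the remedy covers.** Extended recruitment starts above 10 % missing and refers to primary outcome values only. It restores the number of patients. It does not bring back the patients who left, so any selection among those analysed remains. The passage gives no corresponding remedy for missing 3-month data.

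**4. Scale.** There is no stated figure to reproduce. The article gives 200 patients, 100 per arm, says that the sample size was not formally calculated, and states no effect size, standard deviation, power or dropout rate. The missing fractions, the 80 % power and the two-sided reading of the 0.05 level below are therefore assumptions.

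*Reference effect.* For means, (1.960 + 0.842) × √(2/100) = 0.396, about 0.40 SD. For proportions it is about 20 points, for example 50 % against 70 %.

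*Best/worst-case range for a difference in proportions.* With a fraction m missing in each arm, the overall difference is (1 − m) × observed difference + m × (difference among the missing). The last term lies between −100 and +100 points before weighting. For an assumed observed difference of 20 points:
- m = 0.10: 0.90 × 20 ± 10 = 8 to 28, a width of 20 points
- m = 0.05: 0.95 × 20 ± 5 = 14 to 24, a width of 10 points

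*Bias in a mean 3-month score.* For one arm this is the missing fraction × the difference between withdrawn and retained patients. If 10 % are missing and that difference is 0.3 to 1.0 SD in one arm only, the bias is 0.10 × 0.3 = 0.03 SD to 0.10 × 1.0 = 0.10 SD, against the 0.40 SD reference. If both arms lose equal shares with equal differences, the bias cancels.

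*Power.* For a true effect of 0.4 SD, power is 80.7 % with 100 per arm and 78.7 %, 76.5 % or 71.6 % with 5 %, 10 % or 20 % lost. At the smaller fractions the loss of precision is modest, so the question is mainly one of selection.

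**The case against.** The strongest reply concerns the primary outcome. A reader might infer that the rule removes patients whose first diagnosis was wrong and so inflates apparent accuracy. One can construct such a case: if 70 of 100 diagnoses are correct and 10 of the 30 incorrect ones are withdrawn, observed accuracy is 70/90 = 77.8 %, about 8 points too high. But this needs all 10 to leave before the expert visit, with no correct case among them, and it shows one arm only. A wrong diagnosis would normally come to light at the expert visit, when agreement is rated, and withdrawal for poor progress under Part II treatment comes later still. The article does not support that chain, and this part of the reply stands.

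It is also true that the 10 % threshold counts missing primary values from every cause, including refusal and non-attendance, and that best/worst-case bounds apply to any missing data. Patients withdrawn by the clinical team who would still give data are an unknown subset. Their number before the expert visit may well be small: acute presentations to emergency services are excluded, and the article expects little missing data. So the figures above show scale and do not measure the effect of this rule.

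The expert visit is a study step to which patients are invited. Nothing says that someone returned to routine care would see that expert, so a rating cannot be assumed to exist in routine records. That stands too, and it shapes the fix.

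Two replies carry less weight. The article is condensed, and the consent form may offer continued data use; but the article states an unqualified rule, which is different from leaving a detail out. Documenting reasons and reporting dropout as a feasibility factor would make the loss visible without recovering any outcome.

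**Conclusion.** The point holds as a worthwhile, inexpensive improvement. The rule ends data collection for patients who may not have refused it, and it conflicts as written with the statements that all patients are assessed by the expert and reviewed at 3 months. It can create avoidable and possibly informative missing data, chiefly in the 3-month comparisons. The agreement outcome is affected only by withdrawals before the expert visit.

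Neither the size nor the direction of any bias follows from the article, because it gives no withdrawal rate and no outcome for those withdrawn. The best/worst-case widths of 20 and 10 points rest on assumed missing fractions of 10 % and 5 % per arm from all causes. A claim that the trial's accuracy estimate is biased upward, or that one arm is favoured, would go beyond the documents.

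**What to change.** Replace the single rule with one that separates stopping study procedures from withdrawing consent to data collection:
- Say explicitly that data already collected are kept.
- Unless the patient refuses, continue to collect the 3-month questionnaires.
- Where the expert assessment has not yet taken place, offer it with the patient's consent.
- Analyse these patients in their randomised arm.
- End data collection only when the patient withdraws consent to it, and record which kind of withdrawal occurred.
- Make the Overseeing experts, Part II and Follow-up wording agree with this rule.

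The clinical criteria for withdrawal stay as they are. The cost is one protocol sentence, one line in the consent form, and a few extra questionnaires or visits to follow up.
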